### Participant Recruitment Timeline

The participants will be recruited from June 2022 to December 2023. As all data will be collected simultaneously, the enrollment process will require only 1 visit from each participant.

#### Sample Size

Based on previous HR variability outcomes reported by Kirkwood and Minas [22], the sample will be composed of 58 participants, considering an effect size of 2.074 (*P*=.04) when a subject believes that an article is true, an attrition level of 10%, and a significance level of 5%.

#### Recruitment

The research team will invite the 58 parents or caregivers in person to participate in the study when they attend the Clinics of Pediatric Dentistry to their children's dental care.

#### Allocation: Sequence Generation and Concealment Mechanism

The study participants will be randomized with randomly selected block sizes using the Sealed Envelope website [30]. For this process, an operator ([name]) will generate a sequence of randomly selected block sizes to randomize participants equally into the test and intervention groups. The allocation sequence will be blinded using opaque, sealed, and consecutively numbered envelopes to ensure allocation confidentiality.

### Data Collection, Management, and Analysis

First, the HR data of the participants will be exported from Polar Ignite 2 and Polar Verity Sense to Microsoft Excel (Microsoft Corporation) as.csv files. Further, the sociodemographic, oral health knowledge, self-perception about information, and eHEALS data will be manually entered into Excel sheets. Moreover, the videos will be exported from the camera and stored in a closed repository for further analysis, according to the findings of Bevilacqua et al [31,32]. Notably, the features were designed based on previous reports regarding the potential to distinguish participants' emotional states [31-34]. As a result, 9 psychophysiological features will be calculated, with 7 related to facial activity and 2 to HR, as summarized in Table 2.

**Table 2 table2:** Description of the psychophysiological characteristics to be measured in the clinical trial.

Feature number	Facial landmark	Description
F_1_	Mouth outer	Monitor the zygomatic muscle
F_2_	Mouth corner	Monitor the zygomatic muscle
F_3_	Eye area	Monitor the orbicularis oculi muscle (eg, blinking)
F_4_	Eyebrow activity	Monitor the corrugator muscle
F_5_	Face area	Monitor facial movement to and away from the camera
F_6_	Face motion	Describe the total distance the head has moved in any direction in a short period
F_7_	Facial COM^a^	Describe the overall movement of all 68 facial landmarks
F_8_	Measured HR^b^	Measurement of HR using Polar Ignite 2 and Polar Verity Sense
F_9_	Remote HR	Estimated measurement of HR using the rPPG^c^ technique

^a^COM: center of mass.

^b^HR: heart rate.

^c^rPPG: remote photoplethysmography.

Features F_1_ to F_7_ are grounded on 68 facial landmarks automatically detected using constrained local neural fields (CLNFs) and are calculated using the Euclidian distance between those facial landmarks [31,32]. However, subjects have unique facial shapes and characteristics, which could prevent their comparison. Thus, we will first calculate a normalization coefficient for the Euclidian distance between the upper and lowermost anchor landmarks to mitigate this problem [31]. Additionally, feature F_9_ is based on remote estimations of HR performed using the established remote photoplethysmography  (rPPG) technique [35]. This is an extremely resilient technique when estimating the HR under challenging conditions and could be combined with the disinformation consumption scenario.

Statistical analysis will be performed using Stata 17.0 software (StataCorp LLC, College Station, TX, USA). The questionnaire and psychophysiological data will be expressed through descriptive analysis (mean, SD, median, minimum, maximum, and percentage of variation). Moreover, the Shapiro-Wilk and Levene tests will be performed to analyze the normality and homogeneity of data to determine significant differences between groups by the Student *t* test (parametric analysis) or Mann-Whitney *U* test (nonparametric analysis). Further, multiple logistic regression models will be developed to evaluate the association of distinct variables with the psychophysiological aspects. Only factors with significant Wald statistics in the simple analysis will be included in the multiple models (*P*<.2). Furthermore, ROC curve analysis will be performed to determine the accuracy of F_9_ concerning F_8_. For all analyses, *P*<.05 will be considered statistically significant.

It is noteworthy that anonymized data will be shared in a public repository after the end of this study.

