#### Outcomes

The primary outcomes will be obtained by comparing the psychophysiological reactions and self-reported emotional states of participants, as well as the self-perception of the utility and truthfulness of the content between the 2 groups.

The secondary outcomes will be related to sociodemographic characteristics, eHEALS scores, and oral health knowledge of the participants, and these are considered possible confounding factors of primary outcomes.

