## Discussion

### Principal Findings

To the best of our knowledge, it is the first study that will evaluate the differences in psychophysiological reactions of internet users exposed to or not exposed to disinformation. Given the proposed hypothesis, we expect that individuals exposed to fluoride-related disinformation will present more psychophysiological reactions during the experiments because of stressors provided by the consumption of novel content. Additionally, those who disagree with the content due to previous health beliefs tend to show more psychophysiological reactions, also considering the cognitive dissonance process [16]. Moreover, it is expected that younger adults with higher levels of eHealth literacy and oral health knowledge probably will feel less persuaded by disinformation than their older counterparts. Finally, we hope to obtain promising results pertaining to the comparison of F_9_ (remote HR) to F_8_ (measured HR), enabling remote validation and measurement of this parameter in future studies on information disorder.

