### Comparison to Prior Work

Notably, the proposed analysis proved effective in detecting remote emotions in experiments with games [31], but it is still necessary to understand its strengths and limitations in the information disorder context. Nevertheless, it could be a precursor to developing artificial intelligence models to detect false health content automatically and prevent consumption in digital environments. In addition, the results can help people who are more susceptible to believe in fluoride-related false messages found on the internet better understand such information.

Furthermore, the present methodology adds a new perspective to the study of information disorder. Currently, this research field focuses on internet-based surveillance of falsehoods on social media to formulate public health measures and policies [24,36,37], besides proposing definitions and taxonomies for a better understanding of this phenomenon [17,38,39]. In this context, previous studies have detected the high prevalence of false or misleading fluoride-related content on distinct social networks [7,24,40,41]. On the other hand, investigations about disinformation concerning the user perspective are still lacking.

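### As written, camera-estimated heart rate (F9) falls among the primary between-arm comparisons, although the watch measures the same heart rate directly (F8) and this trial is itself to establish F9's accuracy

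*Protocol article*

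**What the plan says.** No single sentence calls F9 a primary outcome. Its status follows from three statements in the protocol article.

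- Outcomes: "The primary outcomes will be obtained by comparing the psychophysiological reactions and self-reported emotional states of participants", together with perceived utility and truthfulness, between the two groups. No individual feature is singled out.
- Data Collection, Management, and Analysis: "9 psychophysiological features will be calculated, with 7 related to facial activity and 2 to HR". Table 2 lists F8 (watch) and F9 side by side and describes F9 as "Estimated measurement of HR using the rPPG^c^ technique".
- The same section, on analysis: normality and homogeneity are checked "to determine significant differences between groups by the Student *t* test (parametric analysis) or Mann-Whitney *U* test (nonparametric analysis"), with P<.05 for every analysis and no feature excluded.

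That section also states that "ROC curve analysis will be performed to determine the accuracy of F_9_ concerning F_8". Under Principal Findings the authors write that "we hope to obtain promising results pertaining to the comparison of F_9_ (remote HR) to F_8_ (measured HR), enabling remote validation and measurement" in future work.

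**The concern.** F9 is given two roles that do not fit together: it is the instrument whose accuracy is to be established, and it is part of the primary evidence for H1. It also adds no new construct. F8 and F9 target the same heart rate over the same session. Where they agree, F9 is redundant. Where they disagree, the protocol's own reference is F8.

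The error in F9 may also be related to arm. F9 is derived from the same face video as F1 to F7, which include movement towards and away from the camera (F5) and head motion (F6). The Discussion expects more psychophysiological reactions in the disinformation arm. If movement disturbs the video-based estimate, the disturbance could be larger in that arm. Randomisation would not balance it, because it arises after exposure. A between-arm difference in F9 that F8 does not show would then be reported as primary support for H1. Adjusting alpha would not cure this, because a systematic error is not a multiplicity problem.

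**Working it through.** **Step 1: is F9 in the primary set?** Outcomes makes the psychophysiological reactions primary. Table 2 lists F1 to F9 as the psychophysiological characteristics. The analysis text applies the group tests to the psychophysiological data without exclusion. Together these include F9. Two passages might take it out:

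- Trial Design names heart rate once, beside seven facial features, but as examples, and it does not say which heart rate.
- Intervention says the Polar Ignite 2 readings go into the analyses, but the alternative there is the backup watch, not the camera.

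Neither removes F9.

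**Step 2: what could a second heart-rate test do?** The protocol gives no figure for the error of F9, its correlation with F8 or its dependence on movement. What follows is a range under assumptions.

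Inputs:
- From the protocol: N = 58, 10% attrition, equal allocation, significance level 0.05. Evaluable: 58 × 0.9 = 52.2, taken as 52, or 26 per arm. In reverse, 52/0.9 = 57.8, which rounds up to 58.
- Assumed: two-sided t test (50 df); one summary value per participant; F8 standard normal with no arm effect; F9 = ρ·F8 + √(1−ρ²)·e, where e is independent standard normal error; a constant shift added to F9 in one arm; ρ from 0.3 to 0.95; 40,000 simulated trials per setting.

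Results (the ranges run over ρ):

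| Shift in F9 (SD) | F9 significant | F9 significant, F8 not | F8 or F9 significant |
|---|---|---|---|
| 0 | 4.9-5.2% | 1.5-4.5% | 6.7-9.5% |
| 0.25 | 14.1-14.4% | 11.3-13.4% | 16.5-18.1% |
| 0.5 | 42.3-42.7% | 39.9-40.5% | 44.7-45.3% |
| 0.8 | 80.6-81.0% | 77.1-78.4% | 82.0-83.5% |

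F8 alone is significant in about 5% of trials throughout, as it should be. If the between-person SD were 10 bpm (assumed), the three non-zero shifts would be 2.5, 5 and 8 bpm.

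**Step 3: reading the first row.** With no artefact at all, F9 is significant and F8 is not in 1.5% (ρ = 0.95) to 4.5% (ρ = 0.3) of trials. A discordant result is therefore not proof of camera error.

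**Step 4: effect of the change.** With F8 as the only primary heart-rate outcome, an F9-only difference can no longer count as primary. The chance of a false heart-rate finding returns from 6.7-9.5% (no artefact) to 5.0%. As a by-product, the nine primary features become eight. If the tests were independent, the chance of at least one false positive would fall from 1 − 0.95⁹ = 37.0% to 1 − 0.95⁸ = 33.7%.

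**The case against.** The strongest reply is that F9's primary status is inferred. The only analysis assigned to F9 by name is the comparison with F8, so the authors may always have meant F8 for the arms and F9 for validation. That is possible, but the text does not say so, and the outcome definition with Table 2 says otherwise.

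The protocol also calls the remote technique established and highly resilient. It standardises the recording through seated posture, a fixed tripod, a spotlight, a white background and high-resolution video. These measures should limit artefact in both arms. They do not settle accuracy, which the trial still sets out to determine.

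Three stronger readings are tempting and should not be drawn:

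- A reader might infer that an F9 difference without an F8 difference can only be camera error. It could also be chance, as the simulation shows, or watch error. A non-significant F8 in 58 participants does not show that true heart rate is equal.
- A reader might infer that arm-related artefact is established. No section predicts a between-arm difference in head movement specifically or gives any error size.
- The remark under Comparison to Prior Work that "it is still necessary to understand its strengths and limitations in the information disorder context" might be read as an admission about remote heart rate. It concerns the remote emotion analysis as a whole.

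A rule for F8/F9 disagreement could sit in an analysis plan that is not at hand, so its absence is not held against the protocol. What stands is the outcome set as the protocol itself states it.

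**Conclusion.** The point holds in a limited form. Read together, Outcomes, Table 2 and the analysis text place F9 among the primary between-arm comparisons. It is a second, indirect measure of a quantity that F8 already measures, and its accuracy is a question of this trial. An F9 difference without an F8 difference has several possible explanations, so it should not count as primary support for H1.

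The size of any arm-related error cannot be derived from the protocol. If there is none, the cost is one redundant test, with F9 alone significant in 1.5-4.5% of trials. If there is a shift of 0.25 to 0.8 SD, that share is about 11% to 78%. These figures rest on the assumed correlations and shifts, on 26 evaluable participants per arm and on two-sided t tests. The change should be made before the data are analysed; the conduct of the trial is not affected.

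**What to change.** - In Outcomes and Table 2, state that F8 is the only heart-rate outcome for the primary between-arm comparison and that F9 is used for validation against F8. Label any between-arm result on F9 exploratory.
- In the validation, report F9 minus F8 by arm and by head movement (F6), so that movement-related or arm-related error can be seen.

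The cost is a change of wording and one further tabulation. F9 no longer counts as a primary result. No directly measured heart-rate information is lost, because the watch is planned to record every participant at 1 Hz with a second device as backup. All the data needed are already planned to be collected.

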Therefore, this study aims to evaluate the patterns of psychophysiological reactions of adults after the consumption of internet-based fluoride-related information and disinformation. The hypothesis (*H_1_*) for this randomized controlled trial indicates that there are differences in the psychophysiological reactions of adults exposed to oral health information and disinformation.

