#### Intervention

The experiments will be conducted based on the methodology described by Kirkwood and Minas [22]. After agreeing with the terms and signing the free consent form, the participants will be led to a silent room and will sit in front of a computer. At this moment, the researcher will instruct the participants about the test functioning (consumption of fluoride-related digital content), highlighting the presentation format and time and explaining the technical issues regarding the capture of psychophysiological reactions, besides encouraging them to persist until the end of the activity, and maintain the sitting posture during the process. To monitor the HR (1 Hz), the participants will be asked to wear 2 digital sports watches (Polar Ignite 2 and Polar Verity Sense) positioned at 7 cm away from their wrists. The HRs captured by Polar Ignite 2 will be used in the analyses, whereas the HRs captured by Polar Verity will be recorded as backup measurements.

Throughout the experiments, a camera (Canon Vixia HF R800 Full HD) will record the participants’ facial expressions. The camera will be placed on a tripod to remain slightly slanted upward and placed to face people at approximately 0.6 m. The video will be recorded in color at 60 frames per second (fps) with a resolution of 1920 × 1080 pixels and saved in the AVCHD-HD format. In addition, a spotlight will be positioned 1.6 m from participants and 45 cm above the camera level to avoid shadows on their faces during the recording. To standardize the recording of the videos, a white photographic background will be positioned approximately 60 cm behind the participants.

Initially, the psychophysiological reaction of participants will be monitored for 150 seconds while they watch a relaxing video with a classical music piece playing in the background (baseline). Next, the monitor will show 25 messages containing fluoride-related information (control) or disinformation (test) in a 6.25-minute slide presentation (15 seconds to read each message).

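### For features F1 to F9, the recorded baseline is not planned as a covariate and the between-arm test is chosen from the data; a prespecified baseline-adjusted model would gain precision at almost no cost

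*Protocol article*

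**What the plan says.** The Intervention section describes three recording windows. The first is the baseline: "Initially, the psychophysiological reaction of participants will be monitored for 150 seconds while they watch a relaxing video". Then come 25 messages at 15 seconds each (25 × 15 s = 375 s = 6.25 minutes). Last, the same video is shown again for 150 seconds so that variation in the parameters can be measured. The camera runs throughout, so the facial features and remote heart rate have a baseline as well as the watch-measured heart rate.

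The statistical paragraph of Data Collection, Management, and Analysis then says that "the Shapiro-Wilk and Levene tests will be performed to analyze the normality and homogeneity of data", and that this serves "to determine significant differences between groups by the Student *t* test (parametric analysis) or Mann-Whitney *U* test (nonparametric analysis". The Abstract and Trial Design repeat the same approach. No section enters the baseline value as a covariate. A percentage variation is listed among the descriptive statistics, and the scale of the tested variable is not stated. The normalization coefficient for the facial landmarks corrects for face shape, not for resting level. The logistic models concern other variables screened at P<.2 and do not name baseline.

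**The concern.** The psychophysiological reactions are among the primary outcomes, and the sample is small. If a post-only value is tested, variation between people that the baseline could explain stays in the error term. A chance baseline difference between arms also passes, multiplied by r, into the estimated effect.

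The choice of test raises a second issue. For each feature, the trial data decide whether a mean difference or a rank comparison is reported, so the estimand is not fixed in advance. If Levene's test fails, the only alternative named is Mann-Whitney, which does not cure unequal variances.

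Both are objections to a method that the article states three times, not to detail that it leaves out.

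**Working it through.** **Inputs from the document.** Total N is 58 with 10% attrition and a 5% significance level (Sample Size). Allocation is equal (Allocation section). The hypothesis is non-directional (Introduction: "there are differences in the psychophysiological reactions of adults exposed to oral health information and disinformation"), so two-sided tests are assumed. Analysed: 58 × 0.9 = 52.2, or about 26 per arm.

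**Inputs assumed.** Power of 80% (none is stated), the correlation r between baseline and outcome (none is given; a range is shown), and equal SDs at baseline and outcome.

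**The plan's own figure.** N = 58 does not follow from the stated inputs. The article sizes the trial "considering an effect size of 2.074 (*P*=.04) when a subject believes that an article is true". Read as a standardized difference, 2.074 needs only 6 to 18 participants before attrition by the normal approximation (one- or two-sided, power 80% to 99%), or 7 to 20 after it. The figure of 58 is matched by inputs that the article does not state: d = 0.8, 80% power and a two-sided t test give 52, and 52/0.9 = 57.8, rounded up to 58. This is a separate matter. Only the 26 per arm is used below.

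**Starting point.** A two-sided 5% t test with 26 per arm has 80% power for a difference of 0.79 SD (noncentral t, 0.792).

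**Variances, with the post-only test set to 1.**
- ANCOVA: 1 − r²
- Change score: 2(1 − r)
- ANCOVA relative to change score: (1 − r²) / [2(1 − r)] = (1 + r)/2

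The detectable difference is 0.792 × √variance. The ANCOVA figures use 49 rather than 50 degrees of freedom (52 − 3 against 52 − 2).

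| r (assumed) | ANCOVA variance vs post-only | Detectable, ANCOVA (SD) | Detectable, change score (SD) | ANCOVA variance vs change score |
|---|---|---|---|---|
| 0.3 | 0.91 | 0.76 | 0.792 × √1.4 = 0.94 | 0.65 |
| 0.5 | 0.75 | 0.69 | 0.792 × √1.0 = 0.79 | 0.75 |
| 0.7 | 0.51 | 0.57 | 0.792 × √0.6 = 0.61 | 0.85 |
| 0.8 | 0.36 | 0.48 | 0.792 × √0.4 = 0.50 | 0.90 |

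For a true difference of 0.5 SD, power is 42% post-only. With ANCOVA it is 46%, 53%, 70% and 84% at the same four values of r. These formulas do not cover a percentage change exactly.

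**Chance imbalance.** The standard error of the baseline difference is √(2/26) = 0.28 SD. A normally distributed feature exceeds this, in one direction or the other, in about a third of trials. At r = 0.7 a post-only comparison carries 0.7 × 0.28 = 0.19 SD of such an imbalance into the arm difference.

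**Test choice under the null.** In 5,000 simulated trials per scenario the two-stage rule rejected 5.1%, 5.9% and 6.1% at SD ratios of 1, 2 and 3; Welch's test rejected 4.9%, 5.5% and 5.0%. In a separate set of 20,000 trials with identical arms and 26 per arm, the rule rejected 5.1% for normal and 5.1% for lognormal data. It led to the t test in 86% of the normal trials and 11% of the lognormal ones. The error rate barely moves, but the quantity reported does.

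**The case against.** The strongest reply is that the article never says the tested value is post-only. It labels a baseline, repeats the same video to measure variation, lists a percentage variation and calls the outcome a reaction. A change-score analysis fits all of this, and a condensed article may leave the derivation of the variable to a fuller document. This stands. A reader might infer that the baseline is used only descriptively, but the document does not fix that.

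A reader might also infer a dramatic gain: at r = 0.9 the detectable difference falls from 0.79 to 0.35 SD, as if 52 participants were 52/0.19 = 274. That holds only against a post-only test. A change-score test at r = 0.9 already detects 0.792 × √0.2 = 0.35 SD, and ANCOVA then saves only (1 − 0.9)/2 = 5% of the variance. Nor does the document give any r. Two of the facial features are movement measures, for which r could be low, and at r = 0.3 the saving against a post-only test is 9%.

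Third, under randomisation an unadjusted comparison is valid. Chance imbalance is not bias and is already reflected in the standard error. The pre-test cannot be called a type I error problem on rejection rates of 5% to 6%.

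The reply does not remove the stated choices: no covariate is planned, and the trial data select the test. Under the equal-SD assumption, ANCOVA's residual variance is no larger than that of either simple analysis, whichever scale was meant.

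**Conclusion.** The point holds as an improvement in efficiency and prespecification for F1 to F9. It does not show that the planned test is invalid. Against a post-only test the variance saving is 9%, 25%, 49% and 64% at r = 0.3, 0.5, 0.7 and 0.8. Against a change score it is 35%, 25%, 15% and 10%. These figures rest on 26 analysed per arm, a two-sided 5% level, equal SDs and an assumed r, which may differ between heart rate and the facial features. For the test choice, the defect is that the data decide between a mean difference and a rank comparison. The emotional-state, utility and truthfulness items fall outside the point: they are binary and are asked only after exposure.

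**What to change.** For each of F1 to F9, replace the test-selection sentence with a prespecified model:

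- Primary comparison: a linear model of the exposure-window mean on arm and the same feature's 150-second baseline mean. State the scale and the window.
- Report the adjusted difference with a 95% CI from heteroscedasticity-robust (HC3) standard errors, which deals with unequal variances directly.
- Apply the same model to the 150-second post-exposure window as a separate analysis.
- Drop the Shapiro-Wilk and Levene gate. If residuals are heavily skewed, add a log-scale analysis or a permutation P value for the same model as a sensitivity analysis.
- Keep a separate analysis for the binary questionnaire outcomes.

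The cost is one degree of freedom, a change of wording and a little analysis work. The baseline recordings are already planned for every participant, so no new data, participants or procedures are needed.

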#### Questionnaires

The participants will respond to a questionnaire containing 6 questions about the self-perception of the emotional state besides the utility and truthfulness of messages, as detailed in Table 1.

Furthermore, as it is expected that age, levels of education, electronic health literacy, and oral health knowledge can influence the ability of participants in acquiring and criticizing digital content [25,26]; these outcomes will be determined through specific questionnaires.

eHealth literacy is defined as the ability of a person to search, find, understand, and evaluate digital health information and apply the acquired knowledge to address or solve a health issue [27]. It will be measured by the Brazilian version of the eHealth Literacy Scale (eHEALS) [28]. This instrument consists of 8 items linked to the consumption of health information on the internet, as demonstrated in Textbox 1. Participants must answer each question according to their self-perception using a 5-point Likert scale that has options varying from “completely agree” to “completely disagree,” with a total score ranging between 8 and 40 points [28].

The participants’ oral health knowledge will be assessed using the questionnaire proposed by Vilella et al [29], which measures knowledge related to topics of interest in pediatric dentistry, such as breastfeeding, sugar intake, bottle feeding, oral hygiene, and use of fluoride toothpaste (Textbox 2). Questions will be answered using a 3-point Likert scale, categorized as “completely agree,” “neither agree nor disagree,” and “completely disagree.” It should be noted that only the “completely agree” option is precise. Hence, the participants receive a point for each correct answer, with a final score ranging between 0 and 9.

Moreover, the participants will answer questions about their sociodemographic characteristics, self-perception of their oral and general health, and use of internet-based health information.

**Table 1 table1:** Questionnaire about self-perception of the emotional state of participants, as well as the utility and truthfulness of messages after the consumption of fluoride-related content.

Question category		Answer options

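### The blanket P<.05 rule also covers loosely specified factor-association models, where a chance significant factor is likely; these models should be labelled exploratory

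*Protocol article*

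**What the plan says.** Under Data Collection, Management, and Analysis, the Protocol article plans two kinds of inference. The first compares the arms by t test or Mann-Whitney test. The second looks for participant characteristics that go with the reactions: "multiple logistic regression models will be developed to evaluate the association of distinct variables with the psychophysiological aspects". Entry to these models is by a screen on the same data: "Only factors with significant Wald statistics in the simple analysis will be included in the multiple models (*P*<.2"). One rule closes the paragraph: "For all analyses, *P*<.05 will be considered statistically significant". The Abstract and Trial Design repeat the screen and the rule in nearly the same terms.

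On the response side, the same section states that "9 psychophysiological features will be calculated, with 7 related to facial activity and 2 to HR". On the factor side, Questionnaires names four: "it is expected that age, levels of education, electronic health literacy, and oral health knowledge can influence the ability of participants". It then adds an uncounted set: "Moreover, the participants will answer questions about their sociodemographic characteristics, self-perception of their oral and general health, and use of internet-based health information". Outcomes gives the factors a status but says nothing about the models: "The secondary outcomes will be related to sociodemographic characteristics, eHEALS scores, and oral health knowledge of the participants". The same sentence also calls them possible confounders of the primary outcomes.

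**The concern.** The article is not silent on error control for these models. It says that any P below .05 counts as significant, and it applies this to a set of tests whose size it does not limit. No factor is matched to a feature, no association is ranked first, and nothing marks the models as exploratory.

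With four named factors and nine features, one model per feature already means 36 tests. Followed as written, the plan is likely to yield at least one significant participant factor even if none is related to any reaction. In a trial about how people react to false health messages, such a factor could be published as a finding about who reacts and who does not.

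A second, separate issue is that the P value printed in a multiple model belongs to a factor already chosen for its small P value in the same people.

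**Working it through.** **Plan's own figure.** The article states no familywise or any-false-positive rate, so there is none to reproduce.

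**Inputs from the article.** 58 participants with 10% attrition (Sample Size): 58 × 0.9 = 52.2, taken as 52 evaluable. Nine features, an entry screen of P<.2 and a significance level of P<.05 (Data Collection, Management, and Analysis). Four named factors plus an uncounted set (Questionnaires).

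**Assumptions, not in the article.** One logistic model per feature; each feature cut at its median so that logistic regression can be run; continuous factors; 3 to 8 factors in total; correlation 0 to 0.9 between features and 0 to 0.3 between factors; two-sided Wald tests.

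**Step 1: independent tests, no screen.** With k factors there are 9k tests, and the chance of at least one P<.05 under no association is 1 − 0.95^(9k):
- k = 3: 1 − 0.95^27 = 75.0%
- k = 4: 1 − 0.95^36 = 84.2%
- k = 6: 1 − 0.95^54 = 93.7%
- k = 8: 1 − 0.95^72 = 97.5%

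**Step 2: the stated two-stage procedure, simulated under no association.** n = 52, nine median-split features, simple logistic Wald P<.2, then multiple logistic Wald P<.05, 600 replicates per setting. The Monte Carlo standard error is at most √(0.5 × 0.5/600) = 2 percentage points. Each cell gives the chance of at least one significant factor, with the expected number of false associations in brackets.

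| Factors | All independent | Feature corr. 0.5, factor corr. 0.3 | Feature corr. 0.9, factor corr. 0.3 |
|---|---|---|---|
| 3 | 69% (1.12) | 53% (0.91) | 38% (1.00) |
| 4 | 76% (1.56) | 62% (1.21) | 45% (1.14) |
| 6 | 89% (2.24) | 74% (1.78) | 57% (1.74) |
| 8 | 95% (3.03) | 78% (1.96) | 65% (2.10) |

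The range is 38% to 95%, or roughly 40-95%.

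**Step 3: what the screen does.** The same simulation with and without the screen, n = 52, factor correlation 0.3:
- 4 factors, feature correlation 0, 0.5, 0.8: 67%, 62%, 48% screened; 80%, 75%, 63% with all factors kept.
- 6 factors, same settings: 78%, 69%, 63% screened; 93%, 89%, 80% with all factors kept.

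The screen lowers the any-false-positive rate. Nor does it raise the unconditional rate per factor-feature pair: 1.56/36 = 4.3% (four factors, all independent) and 1.96/72 = 2.7% (eight factors, correlated). The number of tests is what produces the high figures in Step 2.

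**Step 4: the P value after selection.** For a single null factor with a uniform P value, P(P<.05 given P<.2) = 0.05/0.20 = 25%. In the simulated multiple models the corresponding rate is 14-23%. As a rough check, if about 20% of null factors enter, 1.56/(36 × 0.20) = 22% and 1.96/(72 × 0.20) = 14%. A null factor that appears in a multiple model therefore reaches P<.05 about 14-23% of the time, not 5%.

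**The case against.** The strongest objection is that the test count is a construction. The article does not say that each feature gets its own model, how a continuous distance or heart rate becomes a binary response, how many factors enter, or whether study arm is among them. Remote heart rate also has its own purpose, validation against measured heart rate. This stands. It means that any percentage must be given as a range under stated assumptions, and that no single figure can be attributed to the plan.

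A reader might infer that the P<.2 screen inflates the error. Step 3 shows that it does not; its only fault here is that it makes the printed P value conditional on selection.

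A reader might also set the 40-95% against the stated 5% and call it a many-fold breach. The article's 5% reads as a level per test and claims no familywise control for these models, so the two are not comparable.

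Nor are these models shown to be tests of the Discussion's susceptibility expectation. Principal Findings says that "it is expected that younger adults with higher levels of eHealth literacy and oral health knowledge probably will feel less persuaded by disinformation", but persuasion is not one of the nine features. The same section does expect more reactions in people who disagree with the content, so it would be too strong to say that no association is anticipated; that expectation is simply not tied to a feature or a model.

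Finally, hierarchy and labelling of supporting models are commonly left to a full analysis plan, and a per-test 5% for covariates is common practice. That disposes of any complaint about omission alone. It does not dispose of the sentence that is on the page, which extends the significance rule to every analysis.

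**Conclusion.** The point holds in a limited form. The article calls P<.05 significant in all analyses, including logistic models of an unspecified set of factors against nine features. Under the assumptions listed above, the chance of declaring at least one factor significant when none matters is roughly 40-95%. The low end needs few factors and highly correlated features; the high end needs about eight factors with everything independent. With the four named factors alone, the tabulated settings give 45-76%. Final-model P values for factors that passed the screen are also conditional on selection.

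A reader might infer that the trial's main result is compromised. It is not: the between-arm primary comparisons do not pass through these models. This is a cheap improvement to what may be claimed from the supporting analyses.

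**What to change.** In Data Collection, Management, and Analysis, and in the matching sentences of the Abstract and Trial Design:

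- Limit the P<.05 rule to the between-arm analyses.
- State that the factor-association models are exploratory, and report their estimates with 95% confidence intervals and no significance claims.

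If the sponsor wants a confirmatory statement about participant factors, name a few of them against one named outcome, enter them together without the P<.2 screen, and test them with Holm at 5%. With three factors, for example, the ordered P values would be compared with 0.05/3 = 0.0167, 0.05/2 = 0.025 and 0.05.

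The cost is one or two sentences, with no extra data or participants. The downside is that a true but modest association would be reported only as hypothesis-generating. The narrower rule would also no longer cover the ROC analysis of remote against measured heart rate, so any test wanted there needs its own sentence.
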